## Abstract

**Background:**

Cognitive frailty is a risk for many adverse health outcomes that are commonly observed in older people. Physical activity is known to be effective to reserve cognitive frailty but the prevalence of physical inactivity is still high in older people. E-health enhances behavioural change effects through an innovative way to deliver behavioural change methods that can enhance the behavioural change effects. However, its effects on older people with cognitive frailty, its effects compared with conventional behavioural change methods, and the sustainability of the effects are unclear.

**Methods:**

This study employs a single-blinded, two-parallel-group, non-inferiority, randomized controlled trial design with a 1:1 group allocation ratio. Eligible participants are aged 60 years or above, have cognitive frailty and physical inactivity, and possess a smartphone for more than six months. The study will be conducted in community settings. In the intervention group, participants will receive a 2-week brisk-walking training followed by a 12-week e-health intervention. In the control group, participants will receive a 2-week brisk-walking training followed by a 12-week conventional behavioural change intervention. The primary outcome is minutes of moderate-to-vigorous physical activity (MVPA). This study aims to recruit a total of 184 participants. Generalized estimating equations (GEE) will be used to examine the effects of the intervention.

**Ethics and dissemination:**

The trial has been registered at ClinicalTrials.gov (Identifier: NCT05758740) on 7th March 2023, https://clinicaltrials.gov/ct2/show/NCT05758740, and all items come from the World Health Organization Trial Registration Data Set. It has been approved by the Research Ethics Committee of Tung Wah College, Hong Kong (reference number: REC2022136). The findings will be disseminated in peer-reviewed journals and presented at international conferences relevant to the subject fields.

**Trial registration:**

The trial has been registered at ClinicalTrials.gov (Identifier: NCT05758740) and all items come from the World Health Organization Trial Registration Data Set. The latest version of the protocol was published online on 7th March 2023.

## Introduction

### Background and rationale

Cognitive frailty is the co-existence of physical frailty and mild cognitive impairment (MCI) [1]. It is more closely associated with adverse health markers (e.g. depression and malnutrition) than MCI or physical frailty [2]. Cognitive frailty is common in community-dwelling older people with a prevalence rate of 8.7% in Hong Kong [3]. The global prevalence is increasing from 6% during 2012–2017 to 11% during 2018 and 2020 [4]. Cognitive frailty is a risk for many adverse health outcomes, such as dementia, dependency and mortality [5]. However, cognitive frailty is considered to be possibly reversible with effective interventions [6, 7]. The probability of reversibility is higher at an earlier stage, thus timely intervention is essential [8].

Physical activity plays a significant role in reversing cognitive frailty [9]. It is because physical activity breaks the vicious cycle between cognitive frailty and physical inactivity by alleviating the pathological conditions of cognitive frailty (e.g. inflammation, glucose metabolism, sarcopenia, and insulin resistance) [10–12]. Weekly 150 min of moderate-to-vigorous physical activity (MVPA) shows additional benefits compared with sitting and light physical activity [13]. Although the benefits of MVPA are promising, physical inactivity remains common in older people, with a prevalence rate of over 60% in the USA and over 40% in Hong Kong and China [14–16]. Physical inactivity in older people is defined as performing fewer than 150 min of moderate-to-vigorous physical activity (MVPA) per week by the World Health Organization [17]. Prevalence of physical inactivity in older people increases with age and level of cognitive impairment [18, 19]. MVPA can reduce the risk of worsening cognitive frailty and improve cognitive and physical functions [7, 20, 21].

Conventionally, a range of behavioural change techniques, standardized by the Coventry, Aberdeen, and London – Refined (CALO-RE) taxonomy (e.g. goal-setting, self-monitoring) and delivered by human interventionists, have been used to promote physical activity [22]. However, the conventional behavioural change interventions that have proven to be effective with younger people are less effective with older people [23]. E-health provides an alternative delivery method to conventional behavioural change methods delivered by human interventionists [24]. E-health uses persuasive technology methods delivered by computer interventionists that potentially enhance behavioural change effects [25]. Systematic reviews showed that e-health technologies increase physical activity in older people with a large effect [26–30]. Albeit the fact that e-health can more effectively promote desirable behaviours (e.g. MVPA), its effects are unknown in the context of vulnerable population (i.e. older people with cognitive frailty) and sustainability, and in comparison with conventional behavioural change interventions.

### Objectives

This study aims to compare the immediate and sustained effects of an e-health intervention and a conventional behavioural change intervention in older people with cognitive frailty in (1) improving MVPA, (2) reducing cognitive frailty, (3) improving cognitive function, (4) improving physical performance, and (5) improving physical activity motivation.

### Trial design

This study employs a single-blinded, two-parallel-group, non-inferiority, randomized controlled trial.

## Methods

This study trial protocol reports the methods following the Standard protocol Items: Recommendations for Interventional Trial (SPIRIT) 2013 guideline [31].

### Study setting

This study will be conducted in community settings. Participants will be recruited from community centres for older people in Hong Kong, including District Elderly Community Centre (DECC) and Neighbourhood Elderly Centre (NEC). All of the community centres for older people in Hong Kong regularly provide recreational social activities for community-dwelling older people aged 60 years or above [32].

### Eligibility

#### Inclusion criteria

Aged 60 years or above;Cognitive frailty, defined as the co-existence of MCI and frailty at either the pre-frail or the frail level [33–35];Physical inactivity, defined as < 150 min of MVPA every week in the 4 weeks preceding the study, as confirmed by a Rapid Assessment of Physical Activity (RAPA) score of ≤ 4 (i.e. regularly underactive) [17, 36]; andPossession of a smartphone on which Samsung Health and WhatsApp can be installed for > 6 months

#### Exclusion criteria

Impaired mobility caused by conditions that require medication (e.g. severe arthritis) and inability to walk briskly outdoors, as defined by a modified Functional Ambulatory Classification score of < 7) [37];Depressive symptomatology, as defined by a Geriatric Depression Scale (GDS) score of ≥ 8 [38];Probable dementia, as defined by a Montreal Cognitive Assessment (MoCA) score of < 20 [39];Physically unfit because of chronic illness, as defined by a Physical Activity Readiness Questionnaire (PAR-Q) score of ≥ 1, and certified by a medical doctor as not physically fit to participate in brisk walking [40]; orEnrolled in other interventions to promote physical activity or training.

### Interventions

#### Intervention components

There are three intervention components: (1) brisk walking training, (2) a conventional behavioural change intervention, and (3) an e-health intervention, as shown in Table 1. All of the intervention components will use various behavioural change techniques (BCT), as specified by CALO-RE taxonomy [41].

**Table 1 Tab1:** Intervention content summary

Component	BCTs	Materials	Procedures	Who	How	Where	Duration	Frequency	Duration
Brisk-walking training	Information provision	BW package	Lecture	RA	F2F	Community centres	1 h	2 times/week	2 weeks
	Demonstration		Demonstration			Outdoor parks			
CBCI	Goal setting Prompts Self-monitor Social support Information provision	CBCI manual	PA counselling	RA	F2F	Community centres	1 h	1 time/week	12 weeks
		PA logbook							
E-health	Goal setting Prompts Self-monitor Social support Information provision	E-health manual	PA counselling	RA	Remote	Self-determine	1 h	1 time/week	12 weeks
		Smartphone		Smartphone					

*BW package* Hong Kong Leisure and Cultural Services Department Brisk Walking Training Programme package, *CBCI* conventional behavioural change intervention, *PA* physical activity, *RA* research assistant, *F2F* face-to-face

##### Brisk walking training

As shown in Table 1, two BCTs are used: (1) information provision and (2) demonstration. We adopt these two BCTs because the Brisk Walking Training Program provided by the Leisure and Cultural Services Department, Hong Kong Government used only these two BCTs [42]. This study follows the contents of this programme to implement brisk walking training. A trained research assistant will deliver face-to-face lectures at the community centres and conduct face-to-face training in outdoor parks proximal to the participants’ homes, such that the participants can practise brisk walking daily. Each training session will last for 1 h and sessions will be conducted twice a week for 2 weeks.

##### Conventional behavioural change intervention

As shown in Table 1, five BCTs are used: (1) goal setting, (2) self-monitoring, (3) prompts, (4) social support, and (5) information provision. The conventional behavioural change intervention employing these five BCTs is based on our pilot study that it shows favourable outcomes on the amount of MVPA, cognitive function, frailty and physical functions [6]. This study follows the physical activity counselling contents (i.e. motivational interviewing, regular social support) using the five BCTs to implement the conventional behavioural change intervention following a standardized procedural manual used in the pilot study [6]. Physical activity logbooks will be used to record and monitor the participants’ physical activity performance and levels. A trained research assistant will deliver group-based conventional behavioural change intervention face-to-face at the community centre with groups of 5–8 participants. Each session will last for 1 h and will be conducted once a week for 12 weeks.

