WhatsApp is a freeware application that allows users to send text messages and voice messages, make voice and video calls, and share images, documents, user locations and other content. It will assist the research assistant in delivering the e-health intervention through *goal setting*, *self-monitoring*, *prompts*, and *social support*. The research assistant will be able to read the participants’ activity records logged by Samsung Health and shared by the participants. *Goal setting* will be tailored to the participant’s individual capabilities. If the participants miss the e-prompts from Samsung Health, the research assistant will *prompt* the participants to attend to the e-prompts and perform physical activities following their goals. The research assistant will summarize the past achievements of the participants and provide feedback on their performance to ensure effective *self-monitoring*. The research assistant will group coach participants with similar capabilities (*n* = 5–8) in a WhatsApp group, thus promoting peer *social support* among the participants.

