### Sample size

We adopt a priori power analysis using the Web-based software GLIMMPSE and employ a general linear mixed model [54]. We set the level of significance at 0.05, the power at 0.9, the number of repeated measures at 3 (i.e. T0, T1, T2), the number of groups at 2 (i.e. the intervention and control groups) and the allocation ratio between the two groups at 1:1. To estimate the effects, we estimate the immediate effect of the intervention according to the effect on the primary outcome compared between two groups with the same interventions (i.e. e-health vs conventional behavioural change intervention) as reported in the pilot study of this project [55]. We assume the effects to be sustained until the 6-month follow-up. We estimate that the sample size is 132. We assume a cumulative drop-up rate of 18.1% at T1 and T2 [56]. The total sample size estimated is 184 participants, with 92 participants in each group.

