### Assignment of interventions

All participants will be individually randomized into groups. Permuted block randomization will be used to randomly select block sizes and a group ratio of 1:1 will be used. A random allocation sequence list will be generated by the web-based application Research Randomizer [57]. The process will be conducted by an independent statistician, who will not participate in any other parts of the proposed study. The statistician will assign group labels to the participants based on their sequence of entries referring to the random sequence list, thus ensuring that other members of the research team cannot foresee the group allocations [58].

In the proposed study, only the outcome assessor will be blinded to the group labels, as it will be impossible to blind the participants and interventionists. The group labels will not be revealed to the outcome assessor and will not appear on any documents. The participants, family members and staff of the centres will be prohibited from disclosing the group labels of the participants. It will not be possible to blind the participants or the interventionists. To further minimize the risk of contamination in the same centre, the participants will be instructed to not teach the intervention-related e-health skills (e.g. the self-paced brisk walking training function in Samsung Health) to the participants in the control group. The WhatsApp groups will only be managed by the interventionists, who will forbid non-participants from joining.

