### Statistical methods

Demographic and outcome data at baseline will be reported either as means with standard deviation or as frequencies with percentages based on their level of measurement. Generalized estimating equations (GEE) will be used to separately test the hypotheses on the five outcomes, which are the dependent variables (i.e. MVPA, cognitive frailty, cognitive function, physical function, and physical activity motivation). The independent variables will be the same across all GEEs: group (two categories: intervention and control groups), timepoint (three categories: T0, T1, T2), and group x timepoint. The primary interpretation of the results will be based on the analysis based on the intention-to-treat principle without adjusting for possible covariates [60, 61]. Sensitivity analyses will be conducted and reported to compare the results of different methods of analysis, such as intention-to-treat and per-protocol analyses [62]. The level of significance will be set at 0.05. Missing data will be managed following Jakobsen’s algorithm according to the missing pattern with various methods (e.g. no imputation, multiple imputations) [63].

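### Both arms are delivered in groups of 5–8 that rely on peer support, but the power calculation allows for no delivery-group correlation and the GEE names no delivery-group level

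*Protocol article*

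**What the plan says.** Protocol article, Conventional behavioural change intervention: the research assistant will "deliver group-based conventional behavioural change intervention face-to-face at the community centre with groups of" 5–8, weekly for 12 weeks. Social support is one of the five techniques.

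Protocol article, E-health: the same five techniques are used. "The research assistant will group coach participants with similar capabilities" in WhatsApp groups, also of 5–8, "thus promoting peer *social support* among the participants".

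Protocol article, Assignment of interventions: "All participants will be individually randomized into groups".

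Protocol article, Sample size: "We set the level of significance at 0.05, the power at 0.9, the number of repeated measures at 3", followed by two groups, "the allocation ratio between the two groups at 1:1", and an effect taken from the pilot study and assumed to last to the 6-month follow-up. The result is 132, raised to 184 (92 per arm) for a loss of 18.1%. No ICC, group size or design effect is listed.

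Protocol article, Statistical methods: the independent variables of every GEE are "group (two categories: intervention and control groups), timepoint (three categories: T0, T1, T2), and group x timepoint". The primary analysis is not adjusted for covariates. The section does not say what unit the GEE is clustered on.

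**The concern.** Randomising individuals makes participants independent at baseline. They then share sessions, a coach and peers for 12 weeks, and the intervention theory is that peers change each other's activity, which is the primary outcome. If that theory holds, outcomes within a delivery group are positively correlated after baseline. This applies in both arms, so each arm mean carries more variance than a calculation that treats people as independent allows.

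Two things are at stake. The stated power of 0.9 at 132 would be too high. And if the GEE handles only repeated measures within a person, its standard errors would be too small. The design is declared as non-inferiority, so intervals that are too narrow would make a false non-inferiority claim easier.

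**Working it through.** **Inputs from the protocol:** significance level 0.05 (sidedness not stated; two-sided used here), power 0.90, 132 analysed, 184 recruited, loss 18.1%, delivery groups of 5–8 (mid-point 6.5).

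**Assumed:** ICC of 0.01, 0.05 and 0.10. The protocol gives none.

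**1. The plan's own figures.** The 132 cannot be rebuilt, because the effect, SD and within-person correlation are not printed. I therefore calibrate to it. With 66 per arm, the implied standardised effect is (1.960 + 1.2816) × √(2/66) = 0.564, which returns 66 per arm and 90% by construction.

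For the step to 184:
- 132/0.819 = 161.2
- 132 × 1.181 = 155.9
- 132/0.819² = 196.8
- 132 × 1.181² = 184.1

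Only the last matches. It suggests that 18.1% was applied twice, but the text does not say so, so both readings are carried forward:
- total loss leaves 184 × 0.819 = 150.7
- loss at each visit leaves 184 × 0.819² = 123.4

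**2. Formulas.**
- Design effect: DEFF = 1 + (m − 1) × ICC
- Power with n analysed: Φ(3.2415 × √(n/(132 × DEFF)) − 1.960)
- True size of a nominal 5% test that ignores groups: 2 × (1 − Φ(1.960/√DEFF))

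Example, m = 6.5, ICC 0.05, n = 132: DEFF = 1 + 5.5 × 0.05 = 1.275, with square root 1.129. Power = Φ(3.2415/1.129 − 1.960) = Φ(0.911) = 81.9%. Size = 2 × (1 − Φ(1.736)) = 8.3%.

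**3. Results for m = 6.5.**

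| ICC | DEFF | Power, 132 | Power, 151 | Power, 123 | True size if clustered by person only |
|---|---|---|---|---|---|
| 0 | 1.000 | 90% | 93% | 88% | 5.0% |
| 0.01 | 1.055 | 88% | 92% | 86% | 5.6% |
| 0.05 | 1.275 | 82% | 87% | 79% | 8.3% |
| 0.10 | 1.550 | 74% | 79% | 71% | 11.5% |

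**4. Sensitivity to group size.** From m = 5 to m = 8:
- Power at 132 is 88.9–88.0% at ICC 0.01, 84.1–79.7% at 0.05 and 78.2–70.1% at 0.10.
- The number analysed that is needed for 90% is 138–142, 159–179 and 185–225.
- With a one-sided 5% test and m = 6.5, power at 132 is 88.6%, 82.8% and 76.0%, so sidedness changes little.

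**5. Break-even.** With 150.7 retained, 90% holds while DEFF ≤ 150.7/132 = 1.1416, that is ICC ≤ 0.1416/5.5 = 0.026 (0.035 for m = 5, 0.020 for m = 8). With 123.4 retained, power is already 88% at ICC 0.

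**6. Number of delivery groups.** 184/8 = 23 to 184/5 = 37 (rounded up).

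**7. Sorting by capability.** A simulation used 66 per arm and no shared group effect, with one arm sorted into groups of 6 on a baseline measure correlated 0.5 with outcome. The independence test had a size of 5.3% sorted and 5.4% unsorted. A delivery-group sandwich variance without correction gave 2.5% under sorting. Sorting alone therefore does not inflate the error rate, and it can make a group-clustered variance conservative.

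**The case against.** **The GEE section lists mean-model terms only.** The clustering unit and working correlation of a GEE are separate settings, and the article names neither. A reader might infer that the protocol commits to person-level clustering, so that its intervals are certainly too narrow. The text does not support that: an analysis plan not shown could cluster on the delivery group. The size inflation is therefore conditional. The sample-size half does not depend on this, because that section lists its inputs.

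**The size rests on an assumed ICC.** This stands. The same interventionist delivers both arms from manuals and goals are individually tailored, which may keep the shared effect small. Nor does the text say that group membership stays fixed for 12 weeks. At ICC 0.01 the loss of power at 132 is under 2 points. The design effect is also applied to a single comparison of two means, whereas the planned test is group by timepoint over three measures, so the figures are approximate.

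**Recruiting 184 gives slack.** This stands in part. If 18.1% is total loss, the surplus absorbs an ICC up to about 0.026. If loss applies at each visit, there is no slack. Extra recruits do not repair the size of a test that ignores groups.

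**Sorting by capability.** A reader might infer that forming WhatsApp groups by similar capability worsens the problem. It does not: only a shared effect of delivery raises the variance of the arm mean.

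**Centres.** A reader might also infer that randomisation should have been stratified by centre, or centre added to the model. The protocol does not support that as a correction. Its contamination safeguards presuppose both arms within a centre, unstratified permuted blocks are valid, and the unadjusted primary model is a deliberate choice.

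**Conclusion.** The point holds for the sample size and conditionally for the analysis. With delivery in groups of 5–8 and peer support as a technique in both arms, a positive within-group correlation is what the intervention theory predicts, and the listed power inputs ignore it. For any positive value, 132 analysed participants give less than the stated 90%.

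A reader might take 82% as the trial's expected power. The documents do not support that: it needs both an ICC of 0.05, which is an assumption, and exactly 132 analysed. At the same ICC it is about 87% if 151 remain and 79% if 123 remain.

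A true size of about 5.6% to 11.5% applies only if the GEE is clustered by person alone, which the protocol neither states nor rules out.

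**What to change.** 1. Record each participant's delivery-group ID while the groups run, since membership may be hard to reconstruct later.
2. Name the delivery group as the GEE clustering unit, with a small-sample correction to the robust variance (such as Mancl–DeRouen or Kauermann–Carroll) because there are only about 23–37 groups. Alternatively, add a delivery-group random effect. Treat anyone never placed in a group as a singleton cluster.
3. Restate power over a stated ICC range and group size, under both readings of the 18.1% loss, and say which reading is meant.
4. Note in the plan that capability sorting in the WhatsApp groups may raise the observed ICC and make the corrected intervals somewhat conservative.

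The cost is one extra variable and some analysis wording. Intervals become somewhat wider and the stated power less favourable. Randomisation, treatment and visits do not change.

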##### E-health

As shown in Table 1, the same set of BCTs as in the conventional behavioural change intervention is used. However, the BCTs are delivered using e-health methods. The e-health physical activity counselling (i.e. motivational interviewing, regular social support) is based on the one implemented in our pilot study [6]. A trained research assistant will deliver the e-health physical activity counselling through remote coaching and the participants’ smartphones, which will have Samsung Health and WhatsApp installed to serve as computer interventionists and assist the research assistant in delivering physical activity counselling (i.e. e-health methods) following a standardized procedural manual in the pilot study [6]. Because the e-health physical activity counselling is delivered remotely, the participants can self-determine the place where to attend it. Similar to the conventional behavioural change intervention, each session will last for 1 h and will be conducted once a week for 12 weeks. During these 12 weeks, the primary duty of the research assistant will be to train the participants to uptake the BCTs delivered by the computer interventionists (i.e. smartphones) and their peers on WhatsApp to practise and increase the amount of brisk walking gradually. This aims at fostering sustained engagement and regular participation in MVPA via brisk walking even after the 12-week training period.

Samsung Health is a free and commercially available wearable activity tracker installable in smartphones that continually monitors walking behaviours (e.g. steps, walking speed, walking time, brisk walking time) and physical activity (e.g. number of minutes of MVPA). Wearable activity trackers offer a favourable low-cost tool to promote physical activity as evidenced by systematic reviews [43, 44]. It plays the role of a computer interventionist because it automatically coaches users through *goal setting*, *self-monitoring* and *prompts*. Samsung Health can *set goals* for daily physical activity in a tailored manner based on users’ performance in previous weeks. Samsung Health also automatically logs physical activity behaviours (e.g. brisk walking time) to allow users to *self-monitor* their brisk walking and MVPA. Samsung Health also *prompts* users to perform physical activities to achieve goals in line with their patterns of physical activity.

WhatsApp is a freeware application that allows users to send text messages and voice messages, make voice and video calls, and share images, documents, user locations and other content. It will assist the research assistant in delivering the e-health intervention through *goal setting*, *self-monitoring*, *prompts*, and *social support*. The research assistant will be able to read the participants’ activity records logged by Samsung Health and shared by the participants. *Goal setting* will be tailored to the participant’s individual capabilities. If the participants miss the e-prompts from Samsung Health, the research assistant will *prompt* the participants to attend to the e-prompts and perform physical activities following their goals. The research assistant will summarize the past achievements of the participants and provide feedback on their performance to ensure effective *self-monitoring*. The research assistant will group coach participants with similar capabilities (*n* = 5–8) in a WhatsApp group, thus promoting peer *social support* among the participants.

